### Primary objective and outcome

The primary objective is to assess the benefit of coordinated care for reducing disability, compared to usual care, in patients, aged between 18 and 60 years, consulting for subacute or recurrent acute LBP. The primary objective will be measured using the validated French version of the Roland Morris Disability Questionnaire (RMDQ) (20–22). The questionnaire comprises 24 questions and is scored from 0 (without disability) to 24 (with maximum disability). The primary outcome measure is the proportion of patients that has an improvement (lower score) of at least 4 points at 12 months after enrollment.

### Secondary objectives and outcomes

The benefit of coordinated primary care, in terms of patients’ clinical improvement and employment status will also be assessed using the following secondary outcome measures:

The proportion of patients that have improved RMDQ scores by at least 4 points, relative to baseline, at 3 and 6 months after enrollment.The evolution of the RMDQ scores measured at baseline and then at 3, 6, and 12 months after enrollment.The proportion of patients that improved by at least 2 points on the numerical pain scale, relative to baseline, at 3, 6, and 12 months after enrollment. The numerical pain scale is widely used and validated by the French Health Authority (“Haute Autorité de Santé”) (23). The scale is assessed from 0 (no pain) to 10 (maximum pain). In the literature an improvement of 1.5 points is considered to the minimum improvement to be of clinical significance (24).The evolution of the numerical pain scale scores measured at baseline and then at 3, 6, and 12 months after enrollment.The proportion of patients that are “actively employed,” defined as being employed and being at work (not on sick leave), at 3, 6, and 12 months after enrollment. Patients on sick leave will not be considered as being actively employed.The number of days of sick leave during the 12 months after enrollment.The proportion of patients considered as having “improved overall.” Patients will be considered to have “improved overall” if they have improved their RMDQ scores by at least 4 points, improved their numerical pain scale by at least 2 points, and are actively employed. The outcome will be measured at 3, 6, and 12 months after enrollment.The change in the physical and mental quality of life of patients during the study measured using the Short-form 12 (SF-12). The SF-12 consists of physical and mental dimensions. Each dimension has 4 categories measure between 0 and a maximum value of 100. The higher the score the better the quality of life. The SF-12 is extensively used with a validated French version (25, 26). The SF-12 will be measured at baseline and at 3, 6, and 12 months after enrollment.The changes in the anxiety and depression scores of the Hospital Anxiety and Depression Scale (HAS). The HAS comprises 14 items: 7 for anxiety and 7 for depression (27). Each item is scored from 0 to 3. The HAS provides anxiety and depression scores ranging from 0 to 21. The study will use the validated French version and will be completed by patients at baseline and at 3 and 12 months (28).

The benefit of coordinated primary care, in terms of the beliefs, feelings, and satisfaction of patients and healthcare professionals will also be assessed using the following secondary outcome measures:

The changes in the occupational and physical scores of the Fear Avoidance Beliefs Questionnaire (FABQ). The self-administered FABQ evaluates the patient’s fears and beliefs surrounding LBP (29). The validated French version of the FABQ was used during the study (30). The FABQ comprises 16 items divided into two dimensions: the physical (items 1–6) and the occupational (items 7–16). Each item is scored from “0” (completely disagree with the statement) to “6” (completely agree with the statement). Thus, the maximum score is 36 for the physical dimension and 60 for the occupational dimension. The FABQ will be completed by patients at baseline, and at 3 and 12 months.The change in the Patient-Centered Coordination by a Care Team (PCCCT) questionnaire. The PCCCT instrument measures the quality of primary care from the patient’s perspective. The questionnaire is composed of 14 items each scored from 0 to 3 (31). The overall score will range from 0 (worst coordination) to 42 (best coordination). The PCCCT questionnaire will be completed by patients at baseline and at 3 and 12 months.The change in the GPs’ satisfaction with the healthcare provided for their patients’ LBP.The change in the physiotherapists’ satisfaction (only in the Coordinated-care group) with the healthcare provided for their patients’ LBP.

The GPs’ and physiotherapists’ satisfaction will be measured, on a scale from 0 (not satisfied) to 10 (completely satisfied), at the following timepoints: when the cluster is initiated, at 6 months after the 5th patient is included in each cluster, and at the end of the follow up of the last patient in each cluster. The GPs’ satisfaction will be compared between the study groups.

The level of implementation of coordinated primary care (the study intervention) will be assessed using the following secondary outcome measures:

The number of healthcare professionals, in the interventional group, that performed both training sessions.The change in the attitudes and beliefs of physiotherapists (only in the Coordinated-care group) toward LBP. This will be measured using the Pain Attitude and Belief Score (PABS) (32). This instrument assesses treatment orientations (either biomechanical or biopsychosocial). The PABS comprises 36 items: 10 in the biomechanical and 9 in the biopsychosocial dimension. Each item is score using a 6-point Likert scale: 1 (disagree) to 6 (totally agree). This data will be collected when the cluster is initiated, at 6 months after the 5th patient is included in each cluster, and at the end of the follow up of the last patient in each cluster.The change in the attitudes and beliefs of GPs (in both study groups) toward LBP. This will be measured using the biomechanical and biopsychosocial dimensions of the PABS. The GPs will complete the instrument when the cluster is initiated, at 6 months after the 5th patient is included in each cluster, and at the end of the follow up of the last patient in each cluster.The numbers and modes of communication (letters, emails, facsimiles, and telephone calls), in both study groups, between GPs and other healthcare professionals (whether or not they are participating in the study) implicated in the patients’ management.Number of consultations/visits/examinations for patients, in both study groups, according to the type of healthcare professional (GPs, physiotherapists, OP or occupational nurse, rheumatologists, other medical specialists, other paramedical healthcare professionals, osteopaths, emergency room visits, imagery, and other examinations), whether or not the healthcare professionals are participating in the study.

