**Discussion:**

This study will evaluate the benefit of a coordinated multi-faceted strategy in primary care for patients with LBP. Notably whether this approach will alleviate the associated disability, attenuate pain, and promote the maintenance or return to work.

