#### Inclusion criteria

Patients need to meet the following criteria to participate in the study:

Patients aged between 18 and 60 years old.Patients consulting a GP with LBP, defined as a pain situated between the 12th rib and the gluteal cleft. The LBP must be either:

Subacute LBP, defined as back pain lasting between 4 and 12 weeks and preceded by at least 30 days without back pain.Acute recurrent LBP, defined as back pain lasting for less than 4 weeks and preceded by at least 30 days without back pain. The patients must have consulted a healthcare provider for LBP within the previous 12 months.

3. Patients must be employed (but can be on temporary sick leave) at enrollment.4. Patients must have access to occupational health services (working for a company that either has its own OP or a company using shared occupational health services).5. Patients must provide signed consent to participate in the study.6. Patients must be registered with a social security scheme.

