**Collection of patient data**				
Sociodemographic data	X				Medical history (LBP and concomitant conditions)	X			
Details concerning LBP	X	X	X	X
Work and employment data (including sick leave)	X	X	X	X

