### Statistics

Quantitative data will be presented as means with standard deviations and will be compared using Mann–Whitney tests. Qualitative data will be presented as numbers with percentages and compared using Fisher’s exact tests.

For the primary objective, the proportion of patients that have an improved (lower score) of at least 4 points, in the RMDQ, at 12 months after enrollment will be compared in the study groups. The analysis will be performed using a multilevel logistic mixed model that will allow the clustering effect to be considered as random.

Similarly, the secondary outcome measures with binary outcomes compared between the study groups (e.g., the proportion of patients that improved by at least 2 points on the numerical pain scale at 12 months) will be analyzed by multilevel logistic mixed regression models.

Secondary outcome measures assessing changes in a quantitative parameter over time (e.g., the evolution of the RMDQ scores measured at baseline and then at 3, 6, and 12 months after enrollment) will be analyzed using linear multilevel mixed regression models. The individual effect will be included in the cluster effect. Time will be considered as qualitative variables with a varying number of modalities, e.g., 4 modalities for outcomes assessed at baseline, and then at 3, 6, and 12 months, and 3 modalities for outcomes assessed at baseline, and then at 3 and 6 months. The effect of the intervention will be evaluated by including an interaction between the variables for time and for the study group. The effect of the intervention will be assessed at each time point. The increased alpha-risk, due to multiple analyses, will be accounted for using the Bonferroni correction.

For these various multilevel models, the variance–covariance matrices will be considered as unstructured. Missing data will be treated using a set of 10 multiple imputations based on chained equations (38, 39). The analyses will be performed bilaterally with the alpha-risk set at 5%, except in cases where the Bonferroni correction was used. The data will be analyzed on an intent-to-treat basis. Thus, all patients with data will be included in the analysis unless they specifically indicate that they do not want their data analyzed.

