GPs in the interventional group may preferentially include patients with severe LBP instead of enrolling all eligible patients if they consider the intervention to be better than usual care, and that this improved care may benefit patients with severe LBP more than patients with less severe LBP. This phenomenon may also occur in the control group, where GPs may be reluctant to suggest study participation because of the protocol’s constraints, to patients with non-severe LBP. We have examined this issue and will address this by providing continuous support for GPs during the study. Where a significant difference between groups in terms of patient’s LBP status at baseline is observed, we planned to adjust analyses to limit the impact of this bias on the results.

Most studies that have assessed the clinical evolution of LBP have used either pain, incapacity, and/or returning to work to measure the effectiveness of interventions (33, 49). However, from a patient’s perspective, reduced LBP is mainly comprised of three dimensions: attenuated pain, improved functional capacity, and combined with an acceptable quality of life, which includes the capacity to work (24). In our study, we chose perceived disability, considered by patients to be of utmost importance, as our primary outcome measure. However, we have included several secondary outcome measures, including measures to assess pain, quality of life, and the patients’ occupational status—other important facets of LBP.

Currently, in France, primary healthcare professionals, working in the same geographical region, are encouraged to group together in multidisciplinary practices. Our study is consistent with this evolution of primary healthcare, evaluating a coordinated strategy composed of a multidisciplinary team. Moreover, our study allows healthcare professionals in each region to form networks that hopefully will persist after the study has been completed. Consequently, we will cluster randomized GPs in the same region to promote local cooperation among professionals.

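### The work-related secondary outcomes are defined and analysed without work status at enrollment, which is collected and can differ between arms

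*Protocol article*

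**What the plan says.** - **Who enters.** Inclusion criteria: "Patients must be employed (but can be on temporary sick leave) at enrollment". Both starting states are therefore eligible.
- **Work outcomes.** Secondary objectives and outcomes lists three that depend on work. 'Actively employed' is "defined as being employed and being at work (not on sick leave), at 3, 6, and 12 months after enrollment". The second is "The number of days of sick leave during the 12 months after enrollment". The third, 'improved overall', requires an RMDQ gain of at least 4 points and that patients have "improved their numerical pain scale by at least 2 points, and are actively employed". The RMDQ and pain responder outcomes in the same list are measured against baseline; the work outcome is not.
- **Aim.** The Discussion paragraph of the Abstract asks whether the strategy will "promote the maintenance or return to work".
- **Data.** In Table 1 the row beginning "Work and employment data (including sick leave" is marked at baseline and at 3, 6 and 12 months.
- **Analysis.** Statistics says that binary secondary outcomes "will be analyzed by multilevel logistic mixed regression models". It names no baseline covariate for them.
- **Adjustment.** The Discussion says: "Where a significant difference between groups in terms of patient’s LBP status at baseline is observed, we planned to adjust analyses". Work status is not mentioned there.
- **Allocation.** Randomization is by cluster, stratified by region and, in Angers, by time of initiation. It is not stratified by anything related to sick leave.

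**The concern.** Work status at enrollment is the baseline version of the work outcome, and it can be expected to predict later work status and sick-leave days. If the arms differ in the share who start on leave, an analysis that ignores this carries the difference into the result.

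Two features make a difference plausible.

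- **Recruitment after allocation.** Intervention professionals are trained before the study, and the Discussion accepts that providers cannot be fully blinded. It also concedes that GPs in either arm may select by severity. The sample size section anticipates different recruitment levels in the two groups, and one exclusion (an outside physiotherapist whom the patient will not leave) applies to the intervention group only. A GP can readily see whether a patient is on sick leave.
- **Few clusters.** With 20 clusters, chance alone can leave a visible imbalance.

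The conditional rule in the Discussion is a weak safeguard. It uses a significance test to decide whether to adjust, and a trial of this size can miss an imbalance large enough to matter.

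**Working it through.** **The plan's own figures.** The article gives no share on sick leave, no work rates and no sample size for a work outcome, so there is no stated figure to reproduce for this point. The stated 500 patients rest on the primary outcome and can be recovered. For 50% vs 70%, two-sided 5%, 80% power, 93 per arm are needed. The design effect is 1 + ((1 + 0.2²) × 25 − 1) × 0.03 = 1.75. Then 93 × 1.75 = 162.8, and 162.8 / 25 = 6.5, so 7 clusters. Adding one cluster per arm (my assumption about the software) gives 8, and 8 / 0.8 = 10 clusters of 25 per arm. Nothing below changes that.

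**Step 1: shift from an unequal mix, with no treatment effect.** Let s be an arm's share on leave at enrollment, pW the follow-up rate at work for those who started at work, and pS the rate for those who started on leave.

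Arm rate = (1 − s) × pW + s × pS

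Difference between arms = (s₂ − s₁) × (pW − pS)

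Example with 25% vs 35% on leave, pW = 95%, pS = 75%: 0.75 × 95 + 0.25 × 75 = 90.0%, and 0.65 × 95 + 0.35 × 75 = 88.0%. The spurious difference is 2.0 points.

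| Assumed pW / pS | 10-point imbalance | 20-point imbalance |
|---|---|---|
| 95% / 85% | 1 point | 2 points |
| 95% / 75% | 2 points | 4 points |
| 90% / 60% | 3 points | 6 points |

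Within each starting state the two arms have the same rate, so a comparison made within states gives 0. For sick-leave days the same formula holds with mean days in place of rates; no input is available to size it. For 'improved overall' the direction is also unknown, because patients on leave may have more room to improve on RMDQ and pain.

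**Step 2: how large a chance imbalance could be.** Inputs from the sample size section are 250 patients per arm, mean cluster size 25 and coefficient of variation 0.2 (a later paragraph of that section prints 0.02; I use 0.2). I assume a leave share of 30% to 50% and an intraclass correlation for leave status of 0.03 to 0.10.

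SD of the difference = √(2 × s × (1 − s) × DE / 250), with DE = 1 + 25 × ICC

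- s = 30%, ICC 0.03: DE = 1.75, SD = 5.4 points, 95% range ± 10.6 points.
- s = 50%, ICC 0.10: DE = 3.5, SD = 8.4 points, 95% range ± 16.4 points.

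An imbalance of 10 points is therefore within the reach of chance. Selective recruitment would come on top.

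**Step 3: what each source does.** Chance imbalance does not bias the unadjusted estimate on average; it widens it, and it distorts the particular trial in which it occurs. Selective recruitment that differs by arm is a bias, which the standard error does not reflect. Adjustment for starting status helps with both.

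**The case against.** The strongest reply is that this is a condensed article. Covariate lists are commonly left to the analysis plan, and silence is not an error. That stands in part: one cannot say that the models contain only group and cluster, because Statistics gives no covariate list at all. But the outcome definitions are fixed in the text, and so is an adjustment rule that depends on a significance test and does not name work status. That rule can be criticized as written.

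Four stronger readings are tempting, and the documents do not support them.

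- **That the trial cannot separate keeping work from returning to it.** Work and sick-leave data are collected at baseline and at every follow-up, so the split can be made. The pooled outcome simply does not make it.
- **That those at work can only maintain and those on leave can only return.** Over 12 months a patient may go on leave and come back, or return and then have to stay at work. The employment tools in the Interventions section are aimed at prevention as well as return.
- **That pooling is an error because it dilutes.** If 20% to 50% start on leave, a 15-point gain confined to them appears as 0.20 × 15 = 3 to 0.50 × 15 = 7.5 points overall. That is the correct average effect in all enrolled patients, a legitimate target. The abstract's phrase about work does not promise two estimates.
- **That 'improved overall' is faulty because a patient at work throughout meets its work part.** The composite also demands real gains in RMDQ and pain, and requiring work status to improve would shut out everyone already working.

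It is also fair to say that the sizes rest on assumed rates, and that the article leaves LBP status undefined, so work status might be meant to fall under it.

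**Conclusion.** The point holds for the three work-related secondary outcomes: starting work status is available, is left out of their definitions and of the stated analysis, and is not clearly reached by the conditional adjustment. The size is moderate, about 1 to 3 percentage points on 'actively employed' per 10-point imbalance. This rests on assumed follow-up rates that differ by 10 to 30 points between the two starting states. No shift arises if the arms have the same share on leave, and the documents do not show that they will differ. Nor do they fix the direction, since selection toward severe cases is described as possible in both arms. The RMDQ primary outcome and the 500-patient target do not depend on this. It is a worthwhile improvement to secondary analyses, not a threat to the trial's main conclusion.

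**What to change.** 1. State that work status at enrollment (at work / on sick leave) enters as a fixed covariate in the mixed models for 'actively employed', sick-leave days and 'improved overall', regardless of any baseline significance test.
2. Define it as the status before the enrollment consultation. Trained GPs are asked to favor short leave, so leave prescribed at that visit may already reflect the allocation and should not be adjusted away.
3. Say explicitly that sick-leave days are analysed with a model that accepts the covariate. Statistics names Mann–Whitney tests for quantitative data in general and linear mixed models for changes over time, and a single 12-month total fits neither description plainly.
4. Optionally, report the work outcome separately by starting status, labelled descriptive because the sick-leave subgroup will be imprecise.

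**Cost.** Analysis wording, plus a check that the baseline form records status before the visit. The odds ratio becomes conditional on starting status, so adjusted percentages by arm should be shown beside it. Adjustment on two categories does not remove selection on severity within them. The Trial status section reports 41 patients enrolled in May 2023 against a target of 500, so at that date the change could still be prespecified credibly.

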### Data collection

The schedule for collecting patient data is shown in Table 1 and that for collecting healthcare professional data in Table 2.

**Table 1 tab1:** Schedule for collecting patient data.

Study procedures	Study time points			
	Baseline	3 months*	6 months*	12 months*
Delay allowed (days)		−7 to +21	−7 to +21	−7 to +21
**Baseline procedures**				
Verification of eligibility	X			
Providing study information and obtaining signed informed consent	X			
**Collection of patient data**				
Sociodemographic data	X				Medical history (LBP and concomitant conditions)	X			
Details concerning LBP	X	X	X	X
Work and employment data (including sick leave)	X	X	X	X
**Completion of instruments by patients**				
Roland Morris Disability Questionnaire (RMDQ)	X	X	X	X
Numerical pain scale (scored from 0 to 10)	X	X	X	X
Short-form 12 (measure of the physical and mental quality of life)	X	X	X	X
Fear Avoidance Belief Questionnaire (FABQ)	X	X		X
Hospital Anxiety and Depression Scale (HADS)	X	X		X
Patient-Centered Coordination of Care Team (PCCCT) questionnaire	X	X		X
Nordic musculoskeletal questionnaire	X			X

LBP, low back pain.

*A medical visit will not be required for these study time points, since patients’ data will be collected using self-administered questionnaires completed at home.

**Table 2 tab2:** Schedule for collecting healthcare professional data.

Study procedures	Study time points		
	At cluster initiation	At 6 months after the 5th patients is enrolled in the cluster	At the end of follow up of the last patient in the cluster
